## Methods/design

### Study design

A mixed-methods study design will be used to answer our research questions. An RCT will be conducted in which all community residents meeting the study criteria will be allocated to receive either the CP@home intervention or usual care (control). Primary and secondary outcomes will be evaluated using parallel comparisons between the intervention and control groups as well as comparisons within groups before and after the intervention is implemented (i.e., using baseline metrics). Qualitative and quantitative process evaluation will be conducted to assess for efficiency of intervention delivery, participant compliance, participant satisfaction, and ways of improving the intervention. The qualitative and quantitative process evaluation will help to generate information on experiences with the program and how to improve it. This study has been approved by the Hamilton Integrated Research Ethics Board. Any amendments will be submitted to the ethics board for approval and revisions made to the clinicaltrials.gov registry, as appropriate.

### Participants

Participants will reside in one of four Ontario regions participating in the RCT. Each region’s paramedic service will identify eligible participants from the previous month and the list will be updated regularly. To be eligible to participate, individuals must meet at least one of the following conditions:called EMS three or more times in the last 6 months and called at least once within the previous monthcalled EMS for a lift assist within the previous monthbe directly referred by paramedics (identified through usual practice)

Individuals living in long-term care facilities and individuals currently involved in a paramedic home-visit program or other paramedic-led frequent user intervention will be excluded. Participation in the CP@home intervention will be voluntary and participants can withdraw at any time.

### Allocation of intervention

Each week, the paramedic service will generate a list of individuals meeting the eligibility criteria. This will be saved to a shared tracking document on a secure virtual network maintained by the McMaster CP Research Team at McMaster University, Hamilton, Ontario. Once the team verify that a participant meets the inclusion and exclusion criteria, they will be randomly allocated to the intervention or control group. The intervention group will receive the CP@home intervention whereas the control group will receive usual care. See Fig. 1 for study flow diagram.

**Fig. 1 Fig1:**
[figure not shown]
Study flow diagram

We have secured a waiver of consent for both intervention and control participants prior to randomization since all baseline data collected on participants will be from de-identified secondary data sources. Post-randomization, participants allocated to the intervention group can opt out from receiving the CP@home intervention and no identifiable information will be collected from this group. Those who agree to receive the CP@home intervention will be asked to provide consent since individual information will be collected as part of the intervention and evaluation process.

### Sample size

Our sample size was calculated based on the mean difference in the number of ambulance calls between the intervention and control groups in 6 months. The mean number of ambulance calls per frequent user was 5.3 (standard deviation = 5.7) over a 6-month period for a local paramedic service. Using EMS reductions as our primary outcome for the sample size calculation and the *t*-test as our method of analysis, we will need 261 participants per group to detect a 25% difference between groups assuming standard parameters (alpha = 0.05 and power = 0.8). This difference is considered clinically significant, and a change in one call per high user could result in a resource savings of CAD 1626.00 per participant [4].

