**Methods/design:**

An open-label, pragmatic, randomized controlled trial with parallel intervention and control groups will be conducted in four paramedic services in Ontario. The sample size has been calculated as 261 per group for a 25% reduction in ambulance calls. Eligible participants will be frequent callers (three or more calls in 6 months), individuals who call for at least one lift assist, or individuals referred to the program by a paramedic. Individuals will be randomly allocated to receive either the Community Paramedicine at Home (CP@home) program intervention or their usual care (control). Intervention participants will receive up to three visits from a community paramedic, who will conduct health risk assessments, provide health promotion and education, provide referrals to local resources, and fax reports back to the family physician. Data will be collected from administrative databases (e.g., paramedic services), a custom CP@home program database, participant surveys, and key informant interviews. An intention-to-treat analysis will be conducted, including descriptive statistics and multi-level modeling to find factors predictive of primary and secondary outcomes. A thematic analysis will be used to analyze the qualitative outcomes. An economic analysis will consider the cost-effectiveness of the program.

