### Recruiting participants to the program

Hamilton Paramedic Service data indicate that about 1450 patients in a single year would have been eligible for CP@home, if it had existed. Therefore, we are confident that we could recruit enough people from the Hamilton site alone. There are no challenges anticipated with the other sites. We anticipate that identified potential participants will want to take part, as it will give them an opportunity to have a visit from a community paramedic up to three times, and may help to solve their hitherto unsolved health-related issues.

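### The stated 80% power uses frequent-user call rates and makes no stated allowance for the wider eligibility routes or for opt-out after randomisation under intention-to-treat

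*Protocol article*

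**What the plan says.** **Planning inputs.** The Sample size section of the protocol article reports: "The mean number of ambulance calls per frequent user was 5.3", with "standard deviation = 5.7) over a 6-month period for a local paramedic service". Using a *t*-test, it concludes that the trial needs "261 participants per group to detect a 25% difference between groups assuming standard parameters (alpha = 0.05 and power = 0.8"). The abstract repeats this: "The sample size has been calculated as 261 per group for a 25% reduction in ambulance calls".

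**Who is enrolled.** The Participants section gives three alternative routes. Only the first has a call-frequency threshold: "called EMS three or more times in the last 6 months", with at least one of those calls in the past month. The second needs one lift-assist call in the past month. The third is referral by a paramedic, with no minimum number of calls. The abstract lists frequent callers separately from "individuals who call for at least one lift assist, or individuals referred to the program by a paramedic".

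**Who is analysed.** Under Allocation of intervention, consent is waived before randomisation, and afterwards "participants allocated to the intervention group can opt out from receiving the CP@home intervention". Data analysis specifies an intention-to-treat comparison of all participants as allocated, so people who opt out stay in the intervention arm. A per-protocol analysis of programme completers is a sensitivity analysis.

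**Expected uptake.** The Discussion gives no figure, only this: "We anticipate that identified potential participants will want to take part".

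**The concern.** The power statement draws on one population and the trial will analyse another.

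- **Case mix.** The mean and SD are described as those of frequent users, but two of the three eligibility routes require no call frequency. If people entering by those routes call less often, a 25% reduction is a smaller absolute difference, and mixing low and high callers can raise the SD relative to the mean.
- **Opt-out.** Intervention participants who decline receive no programme but count in the intervention arm. If the 25% is what the programme achieves in those who take it up, the difference between randomised arms shrinks in proportion to uptake.

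The Background says the results will inform policy whether or not the programme proves beneficial. With power well below 80%, a null intention-to-treat result could reflect low uptake or case mix rather than an ineffective programme, and the stated 80% would hide that.

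**Working it through.** **Inputs from the Sample size section:** mean 5.3, SD 5.7, 25% difference, alpha 0.05 (taken as two-sided; sidedness is not stated), power 0.80, 261 per group. Uptake and case mix are not given in the document, so the values below are assumptions shown over a range.

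**1. The plan's own figure.** Difference δ = 0.25 × 5.3 = 1.325.

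n per group = 2 × SD² × (1.960 + 0.842)² / δ² = 2 × 32.49 × 7.849 / 1.7556 ≈ 291. The exact *t*-test gives 291.5, i.e. 292.

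The stated 261 is not reproduced. At 261 per group the standard error is 5.7 × √(2/261) = 0.499, the ratio δ/SE is 1.325 / 0.499 = 2.66, and *t*-test power is 75.5%. A difference of 1.4 calls (26.4% of 5.3) does give 261, but the text does not state that difference. Both starting points are carried forward in step 2 so that this discrepancy is not counted as an uptake effect.

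**2. Opt-out, if the 25% applies to acceptors only.** With no effect in those who opt out, the intention-to-treat difference is uptake × δ. SD is held at 5.7, with 261 per group.

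| Uptake (assumed) | Difference from 1.325 | Power | Power if full-uptake difference is 1.4 |
|---|---|---|---|
| 100% | 1.325 | 76% | 80% |
| 90% | 1.193 | 66% | 71% |
| 80% | 1.060 | 56% | 61% |
| 60% | 0.795 | 36% | 39% |

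From the 1.325 start, moving from full to 90% uptake costs about 9 percentage points, and moving to 80% costs about 19.

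**3. Case mix, at full uptake.** Assume half the sample are frequent users at 5.3 (SD 5.7) and half enter by other routes with mean m₂ and SD s₂. The 25% effect applies to everyone.

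Overall mean = (5.3 + m₂)/2.
Overall variance = ½(5.7² + 5.3²) + ½(s₂² + m₂²) − mean².

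- m₂ = 1, s₂ = 2: mean 3.15, variance 22.87, SD 4.78, SD/mean 1.52. Difference 0.25 × 3.15 = 0.788; power 47%.
- m₂ = 2, s₂ = 3: mean 3.65, variance 23.47, SD 4.84, SD/mean 1.33. Difference 0.25 × 3.65 = 0.913; power 57%.

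**4. When case mix does not matter.** For a fixed percentage reduction, power depends on SD/mean, which is 5.7/5.3 = 1.075 in the plan. A lower mean with the same ratio leaves power at about 76%. With half the sample at a mean of 3 and Poisson variation (SD √3), the overall mean is 4.15, SD 4.37 and ratio 1.05, and power is 77%. A smaller share of low callers also costs less: with 25% at mean 2 and the plan's SD/mean ratio, power is 68%.

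**The case against.** **The 25% may already be the intention-to-treat target.** The Sample size section speaks of a difference between groups and calls it clinically significant, in a trial described as pragmatic. That reads naturally as a difference between randomised arms, and on that reading the dilution in step 2 does not apply. This stands as a possible reading. The text does not settle it, and no uptake assumption appears anywhere that would show the 25% had been set with non-uptake in mind.

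**Frequent user may mean the whole study population.** Usage is mixed. The outcome section and Table 1 use the term for the people studied, while the abstract and the Discussion set frequent callers or users apart from lift-assist callers. The Sample size section does not define its source group, so a mismatch is likely but not proven.

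**Uptake will be visible.** Visits are recorded and a per-protocol analysis is planned. This helps interpretation, but that analysis keeps only completers, who select themselves, and it does not restore power. Collecting outcomes from administrative data deals with missing outcomes, not with untreated people in the intervention arm.

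**Stronger readings that the documents do not support.** A reader might infer that the 80% was definitely calculated for treated frequent users only; the text does not say so. A reader might also infer that 5.3 comes from the period that identified these people, so that follow-up calls will be lower and power must fall. The section does not say which 6 months were used, and a lower mean alone does not reduce power if SD/mean is unchanged.

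**Conclusion.** The point holds as a defect in the stated power. The 80% at 261 per group rests on a frequent-user mean and SD, and the plan states no allowance for the two eligibility routes without a call threshold or for opt-outs retained under intention-to-treat.

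- Firm, from the plan's inputs (two-sided test): about 76% power at 261 per group, and about 292 per group for 80%.
- Conditional on the 25% being the effect in acceptors, and on assumed uptake: about 66%, 56% and 36% at 90%, 80% and 60%.
- Conditional on an assumed half-and-half case mix with a mean of 1 to 2 calls in the other half: about 47% to 57% at full uptake. Other plausible mixes cost less or nothing.

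The documents do not establish what power the trial will actually have, because neither uptake nor the call distribution in the enrolled population is given.

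**What to change.** Keep 261 per group and rewrite the power statement in the Sample size section.

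1. Take the control mean and SD from paramedic-service records for people who meet the eligibility criteria, counting calls in the 6 months after identification. Cover every route the records can identify, and name any that they cannot. The Discussion says one participating service's data already yielded a count of about 1450 eligible patients in a year; it does not say whether that count includes paramedic referrals.
2. State whether the 25% is the intention-to-treat difference or the effect in people who accept the programme. If the latter, give intention-to-treat power at stated uptakes, for example 90%, 75% and 60%. On the present mean, SD and 1.325 difference these would be about 66%, 51% and 36%.

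The cost is one data extract and a rewritten paragraph. The downside is that the stated power will probably be less favourable than 80%.

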### Data gathering procedures

The primary and secondary outcomes will be assessed over two time periods: the 6 months prior to the start of the intervention and the 6 months after the initiation of the intervention. Data will be collected from: (1) the local paramedic service databases (EMS call volumes), (2) the CP@home database, which is completed by the community paramedics (health risk assessments, quality of life, other health-related scales, and community referrals), and (3) administrative databases (ED visits, hospital admissions, and primary care visits). Administrative data will be collected pre- and post-intervention, as well as during the study. Table 1 summarizes the outcomes, data sources, and analyses. Data will be transferred from the paramedic services to the study team through a secure, encrypted virtual private network.

**Table 1 Tab1:** Summary of outcomes, data sources, and analysis

Outcome	Data source(s)	Data analysis
Primary		
Number of repeat EMS calls resulting in ambulance dispatch in the study population	Paramedic services administrative data	- Comparison between intervention and control groups after the 6-month intervention - Multi-level modeling of factors affecting outcome
Secondary		
Number of ED presentations in the study population	Hospital and ED database Paramedic services administrative data	- Comparison between intervention and control groups after the 6-month intervention - Multi-level modeling of factors affecting outcome
Number of hospital admissions in the study population	Hospital and ED database	
Number of referrals to community services (intervention group only)	CP@home database Paramedic services administrative data	- Descriptive analysis
Number of referrals to family physicians (intervention group only)	CP@home database Paramedic services administrative data	
Tertiary		
Characteristics of frequent users (baseline only)	CP@home database	- Descriptive analysis
Cost-effectiveness of CP@home	CP@home database Paramedic services administrative data	- Economic analysis
Process		
Number of CP@home visits	CP@home database	- Descriptive analysis - Thematic analysis
CP@home participant satisfaction	Self-administered survey Key informant and individual interviews of participants and paramedics	

*ED* emergency department, *EMS* emergency medical services

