### Data analysis

An intention-to-treat analysis will compare all participants as originally allocated after randomization. This will help to avoid any bias associated with a non-random loss of participants. A sensitivity analysis will compare the results of the intention-to-treat analysis to the per-protocol analysis (which includes only participants who have completed the full program). Outcomes will be analyzed at the individual level and geographic level (e.g., by postal code or ward).

Descriptive statistics will be generated for the baseline demographics. The characteristics of the intervention and control groups will be compared. Correlations statistics will be run between variables. Multi-level modeling will be conducted to find factors predictive of the primary and secondary outcomes. Finally, a thematic analysis of the KIIs and participant feedback surveys will be completed.

Intervention fidelity will be maintained through regular monitoring of the CP@home database (by monitoring referral patterns by EMS personnel and proper use of the screening tools). The main outcomes will be analyzed after completing the participant recruitment process (pre-intervention analysis) and 6 to 9 months after completing the intervention for all participants (post-intervention data and full data analysis).

Both CP@home intervention and health-care resource utilization and costs will be collected for the economic analysis, with a focus on whether the upfront cost of the CP@home intervention is offset by other health-care cost savings [44]. Decision analytic modelling techniques will be used to project final outcomes, like life years and quality adjusted life years, from intermediate outcomes measured during the evaluation period. Our economics team has extensive experience in conducting trial-based and modelling-based evaluations aligned with the needs of health policy makers.

For the quantitative process evaluation, data will be analyzed using frequency and descriptive measures. In the qualitative process evaluation, themes and opinions will be analyzed. A within-case and cross-case analysis will be completed for themes generated to summarize the participants’ and implementers’ experiences with the program.

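### The only between-group test named is a t-test with about 75.5% power at 261 per group, and the baseline call count held for both arms is given no role in the treatment-effect estimate

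*Protocol article*

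**What the plan says.** In the protocol article, Sample size, the basis is the between-group contrast alone: "Our sample size was calculated based on the mean difference in the number of ambulance calls between the intervention and control groups in 6 months". Its inputs are "The mean number of ambulance calls per frequent user was 5.3 (standard deviation = 5.7) over a 6-month period", and the target is set with "assuming standard parameters (alpha = 0.05 and power = 0.8". The t-test is named there as the method: "test as our method of analysis, we will need 261 participants per group to detect a 25% difference". The abstract repeats the figure: "The sample size has been calculated as 261 per group for a 25% reduction in ambulance calls".

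Table 1 (Data gathering procedures) lists two analyses of the primary outcome. One is "Comparison between intervention and control groups after the 6-month intervention", with no test or covariate named. The other is multi-level modelling, whose purpose Data analysis gives as follows: "Multi-level modeling will be conducted to find factors predictive of the primary and secondary outcomes".

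Baseline calls appear in three places. Objectives and research questions asks how repeat calls compare with each person's own baseline. Study design plans before/after comparisons within groups. Data gathering procedures sets a 6-month window before the intervention and one after its start, with call volumes taken from paramedic service databases.

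**The concern.** The number of calls a person made in the previous 6 months is likely to be among the better predictors of the number made in the next 6. If the between-group comparison leaves it out, two things follow.

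- Chance differences between arms in prior call volume pass into the estimate. If the baseline SD is also near 5.7, the standard error of the baseline difference at 261 per group is 5.7 × √(2/261) = 0.50 call. That is 38% of the 1.325-call target.
- Precision already paid for is lost, in a trial whose stated size falls short of its own power target.

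The before/after comparisons do not make up for this. They do not estimate the randomised effect. They are also open to regression to the mean, because one entry route in Participants requires three or more calls within the previous 6 months.

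**Working it through.** **Inputs.** From Sample size: mean 5.3, SD 5.7, 25% difference, alpha 0.05, power 0.8, 261 per group. Sidedness is not stated, so two-sided is assumed. The pre/post correlation r is not given, so a range of 0.2 to 0.7 is assumed.

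**Step 1: the plan's own figure.** Difference = 0.25 × 5.3 = 1.325 calls; standardised effect = 1.325/5.7 = 0.2325.

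- Normal formula: n = 2 × (1.960 + 0.842)² × (5.7/1.325)² = 290.5, so 291 per group. The exact noncentral t gives 291.5, so 292.
- Power at 261: standard error = 5.7 × √(2/261) = 0.499; 1.325/0.499 = 2.655; Φ(2.655 − 1.960) = 75.7%. The exact t gives 75.5%.
- Alternatives do not give 261: one-sided alpha gives 229, and letting the intervention-arm SD shrink with its mean gives 227. A difference of 1.4 calls does give 261 by the normal formula, but 1.4/5.3 is 26.4%, not 25%.

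**Step 2: add baseline calls as a linear covariate.** The residual SD becomes 5.7 × √(1 − r²).

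| Assumed r | Residual SD | Power at 261 (exact t) | n per group for 80% (exact t) |
|---|---|---|---|
| 0 (unadjusted) | 5.70 | 75.5% | 292 |
| 0.2 | 5.58 | 77% | 280 |
| 0.3 | 5.44 | 79% | 266 |
| 0.4 | 5.22 | 82% | 245 |
| 0.5 | 4.94 | 86% | 219 |
| 0.6 | 4.56 | 91% | 187 |
| 0.7 | 4.07 | 96% | 150 |

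Power reaches 80% at r of about 0.32 to 0.33.

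**Step 3: does a count model help by itself?** Matching a negative binomial to 5.3 and 5.7 gives dispersion (5.7² − 5.3)/5.3² = 0.968. With a rate ratio of 0.75 the intervention mean is 3.975 and its SD falls to 4.39.

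- Unadjusted negative binomial: variance of the log rate ratio = (1/5.3 + 1/3.975 + 2 × 0.968)/261 = 0.00910; 0.2877/0.0954 = 3.015; power 85.4%.
- t-test on the same data: standard error = √((5.7² + 4.39²)/261) = 0.445; 1.325/0.445 = 2.975; power 84.5%.

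The difference is about 1 point. Both exceed 75.5% only because the intervention-arm SD is allowed to shrink here, whereas the plan gives one SD.

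**Step 4: simulation at 261 per group.** Negative binomial counts, 600 runs per setting. The t-test had 82 to 85% power throughout. Adding baseline calls (linear or negative binomial model) gave about 86% at an observed correlation of 0.22, 87 to 88% at 0.38, 88 to 92% at 0.55 and 96 to 99% at 0.69. With no true effect, the t-test rejected in 3 to 7% of runs (300 per setting), compatible with 5%.

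**The case against.** The t-test is named in the sample-size paragraph. Sizing a trial on a t-test and analysing it with a model is common practice. Data analysis does not mention a t-test, Table 1 names no test, and the multi-level model could carry both allocation and baseline calls. Distribution, covariates and standard errors are often left to an analysis plan, and that plan is not shown here.

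Much of this stands. A reader might infer that the final analysis is fixed as an unadjusted t-test, or that baseline calls are ignored. The documents support neither: no section says that the primary comparison is unadjusted, and baseline calls do have a planned within-group use. What remains is a matter of stated content. The one method named has no baseline term, the model is described as a search for predictors, and the role given to baseline is within-group.

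A reader might also infer that an SD above the mean disqualifies the t-test. Steps 3 and 4 show that it does not at this sample size.

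Lastly, a simulation can make the gain look very large. One heavy-tailed generator gives about 45% power for the t-test, 74% for linear adjustment and 83% for an adjusted negative binomial model. It matches 5.3 and 5.7 at baseline, but its follow-up counts have a mean of about 4.0, an SD of about 8 to 9 and a correlation near 0.7. It also sends everyone through the three-call route, although Participants admits others after one lift assist or a referral. Those are assumptions, not plan figures, and the result should not be quoted as this trial's power.

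**Conclusion.** The point holds in limited form. The protocol commits to no use of baseline calls in the between-group estimate, and the one test it names falls short of its stated power: 75.5% at 261 per group, against 80%. This assumes a two-sided test and a common SD of 5.7. If the intervention-arm SD shrinks with its mean, unadjusted power is about 84.5%, but then 261 is not the number that the calculation yields either.

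The gain from adjustment depends on an unknown correlation: about 2 points at 0.2, 11 at 0.5 and 20 at 0.7. Selecting people on a high baseline count could lower the correlation, and regression to the mean could bring the follow-up mean below 5.3. The gain comes mainly from the covariate, not from the count distribution. This is an improvement that should be made, not a fault that invalidates the trial.

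**What to change.** Pre-specify one primary between-group model: EMS calls in the 6 months after randomisation on allocated arm, adjusted for calls in the 6 months before randomisation and for paramedic service. A negative binomial model with robust standard errors is one suitable choice. It yields a rate ratio, which matches a target stated as a percentage; the difference in mean calls should be shown alongside. Keep the t-test as supportive and the modelling of predictive factors as exploratory.

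In Sample size, restate unadjusted power at 261 as about 75.5%, or raise the number to 292 per group. If adjustment is relied on to reach 80%, state the assumed correlation and its source. Past call records from a participating service could supply it.

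The cost is wording only: the baseline counts come from administrative data already planned for both arms, and the outcome does not depend on contact with participants (Loss to follow-up).
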